## Methods/Design

### Trial design

The study design adheres to the ‘CONsolidated Standards Of Reporting Trials’ (CONSORT) Statement and the CONSORT extension to non-pharmacological interventions [19]. The research design entails a RCT with multisite recruitment of 135 participants with severe TBI over a 28-month period (4 to 5 participants on average per month). Participants will be recruited on a consecutive discharge basis across two cities (Brisbane and Sydney, Australia) and randomly allocated using matched assignment [20]. Global neuropsychological function is potentially related to pre-intervention functioning [21], and thus the matching process is designed to ensure a relatively equal proportion of individuals in each intervention with mild to moderate and severe neuropsychological deficits. Participants’ global neuropsychological function (mild to moderate or severe deficit subgroups) will be determined prior to the randomization. The use of ELL as an active control intervention is based on both the theoretical significance of comparing outcomes of ELL and EBL and the ethical considerations of providing a ‘credible’ intervention instead of a sham or pseudotreatment [22]. This is important for both the participants and the therapists administering the intervention.

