### Randomization

Participants’ global neuropsychological function (mild to moderate deficit (<−2 SD) or severe deficit (≥ − 2 SD)) will be used to determine their subgroup for random allocation based on matched assignment. The random assignment will be conducted independent of the project staff involved in the interventions and the blind assessor. For each subgroup (that is, mild to moderate or severe deficit), participants will be randomly allocated to EBL or ELL using sequentially numbered and sealed opaque envelopes. The envelopes will contain group allocation on a written insert, based on a predetermined random computer generated sequence [20].

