### Sample size

Our previous RCT findings [14,15] indicated that individualized EBL training was more effective than another active intervention in improving awareness of deficits and behavioral competency between pre-intervention and post-intervention assessment (group × time interaction effects: partial η^2^ = 0.061 to 0.13). Based on a similar design and approach to statistical analysis, a conservative power analysis was conducted using an estimated medium effect size (partial η^2^ = 0.061, PCRS discrepancy score), alpha level of 0.05, and power of 0.8. According to G*Power [40], a sample size of *n* = 123 is required to detect significant effects. Due to possible participant dropout (estimated as 10% from the previous RCT [14]), a total sample size of *n* = 135 will be required.

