### Statistical analysis

Data will be screened to ascertain any state/site or therapist effects or the effects of demographic and clinical factors on outcome, with any significant variables treated as covariates in respective analyses. Participant dropout will be managed on an intention-to-treat basis using the last observation carried forward method, and participants will be analyzed in the group to which they were allocated, irrespective of compliance or withdrawal from treatment [41]. To compare the efficacy of EBL and ELL for improving error self-regulation skills, analysis of covariance (ANCOVA) will be conducted using endpoint means and adjusting for baseline scores for the primary outcome (Cooking Task errors) and secondary outcome (Zoo Map part 1). The estimated effect size and its precision will be examined using a 95 % CI for the mean difference. Mixed 2 × 3 analysis of variance (ANOVA) procedures (grouped by time: pre-intervention, post-intervention and follow-up periods) will examine the impact of each intervention on awareness of deficits, behavioral competency, role functioning and support needs. In the latter analyses, interaction effects will be examined to determine whether EBL is associated with greater gains than ELL relative to pre-intervention functioning. Hierarchical regression will be used to determine whether pre/post changes in awareness, error self-regulation and behavioral competency predict long-term outcomes on the SPRS and CANS after controlling for pre-intervention functioning.

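### Randomisation is stratified by neuropsychological deficit, but the stratum can enter the two ANCOVAs only through a significance screen; the loss is small and the remedy nearly free

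*Protocol article*

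**What the plan says.** The Randomization section makes the design stratified: "For each subgroup (that is, mild to moderate or severe deficit), participants will be randomly allocated to EBL or ELL". The sealed envelopes follow a sequence described as "based on a predetermined random computer generated sequence"; no block size or other restriction is given. The Trial design section gives the reason for choosing this factor: "Global neuropsychological function is potentially related to pre-intervention functioning". It adds that matching is meant to give the two arms roughly equal shares of each deficit level.

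The Statistical analysis section names one covariate for the two error self-regulation outcomes, the baseline score: "analysis of covariance (ANCOVA) will be conducted using endpoint means and adjusting for baseline scores for the primary outcome (Cooking Task errors", with Zoo Map part 1 handled alike. Anything else depends on a screen that comes first in that section: "Data will be screened to ascertain any state/site or therapist effects or the effects of demographic and clinical factors on outcome". What the screen turns up is then admitted by a significance rule, outcome by outcome: "with any significant variables treated as covariates in respective analyses". The deficit stratum is not mentioned. The awareness, competency, role and support outcomes go to group-by-time mixed ANOVAs, and a hierarchical regression relates pre/post changes to long-term outcomes.

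**The concern.** A factor used to stratify the randomisation is part of the design and normally belongs in the model regardless of its p-value. Here the only route into the model is a data-driven test. Because the rule works analysis by analysis, the stratum could be adjusted for in the Cooking Task model and left out of the Zoo Map model, or the reverse.

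Two things could be lost. If the stratum predicts the endpoint beyond the baseline score, leaving it out keeps that variance in the error term and costs precision. If allocation is also forced to balance within strata, the usual standard error overstates the true sampling variation and the test becomes conservative.

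**Working it through.** **Inputs.** From the Sample size section: "estimated medium effect size (partial η^2^ = 0.061, PCRS discrepancy score", "alpha level of 0.05, and power of 0.8", and 123 participants before dropout. From the Primary outcome section: Cooking Task test-retest r = 0.89. Assumed, because the article gives no figure: q, the share of baseline-adjusted endpoint variance explained by the stratum, shown at 0.02, 0.05 and 0.10. The effect size comes from the PCRS discrepancy score, so it carries over to the Cooking Task only by assumption.

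**1. The plan's own figure.** f² = 0.061/0.939 = 0.06496, so f = 0.255 and d = 2f = 0.51. An F test with 1 numerator df and noncentrality N·f² has power 0.7975 at N = 122 and 0.8007 at N = 123. The stated 123 reproduces, with no credit taken for the stratum.

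**2. Always including the stratum, against baseline only.** In closed form, f² becomes f²/(1 − q) and the error df falls to N − 4. Simulation at N = 123 used two strata of equal expected size, with 6,000 runs for power and 15,000 under the null. Each power cell shows baseline-only → with stratum.

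| q | Closed form | Simulated, unrestricted sequence | Simulated, blocks of 4 in strata |
|---|---|---|---|
| 0.02 | 0.8007 → 0.8085 | 0.7942 → 0.7975 | 0.7952 → 0.8012 |
| 0.05 | 0.8007 → 0.8204 | 0.7927 → 0.8082 | 0.8130 → 0.8243 |
| 0.10 | 0.8007 → 0.8403 | 0.8062 → 0.8395 | 0.8022 → 0.8288 |

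The simulated gains are 0.3, 1.6 and 3.3 points with an unrestricted sequence, and 0.6, 1.1 and 2.7 with blocks. The closed form gives slightly more (0.8, 2.0 and 4.0). It ignores chance imbalance under an unrestricted sequence, and it ignores that balance within strata already gives the baseline-only estimate most of the available precision.

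**3. Calibration of the baseline-only model (nominal 0.05).**
- Blocks of 4: type I error 0.049, 0.045 and 0.042 at the three values of q. At q = 0.10 the mean model SE is 0.181 against a true SD of 0.174, an overstatement of about 4%.
- Unrestricted sequence: 0.048, 0.050 and 0.050. At q = 0.10 the SE is 0.1815 against 0.1816. The interval is valid but longer than it need be, by 1/√(1 − q): 1.0%, 2.6% and 5.4%.

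**4. The rule the plan actually states.** Suppose the stratum is among the screened factors and is tested given baseline at 0.05. The noncentrality is N·q/(1 − q) = 2.51, 6.47 and 13.67, so it is selected about 35%, 71% and 96% of the time. In a simulation at N = 124 with forced balance, power for always including against screening is 0.813 v 0.813 at q = 0.03, 0.829 v 0.828 at 0.05 and 0.839 v 0.839 at 0.10. Type I error at q = 0.10 is 0.048 for both. With an unrestricted sequence the gap is at most about half a point.

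**5. Plausible q.** Let the underlying composite correlate g with the score at both times, let ρ be the baseline-endpoint correlation, and let p be the proportion in one stratum. Dichotomising gives s = g·φ(z_p)/√(p(1 − p)), and q = [s(1 − ρ)]²/[(1 − s²)(1 − ρ²)]. With ρ = 0.89, g = 0.5 and p = 0.5: s = 0.399 and q = 0.0439²/(0.841 × 0.2079) = 0.011. Over g = 0.3 to 0.7 and p = 0.2 to 0.5, q runs from about 0.003 to 0.03 at ρ = 0.89, and from about 0.01 to 0.15 at ρ = 0.5 to 0.7.

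**6. The other analyses.** A stratum main effect is constant within a person, so it leaves the group-by-time test unchanged; only a stratum-by-time term could help. The hierarchical regression is not described as an arm comparison.

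**The case against.** The strongest reply is that the plan is not a baseline-only plan. Global neuropsychological function reads naturally as a clinical factor, so the screen would usually admit it when it matters, and little is lost when it does not. Step 4 bears this out on power, and that part stands. A reader might infer from the ANCOVA sentence alone that the stratum is excluded; the screening sentence rules that out.

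A reader might also infer that the confidence intervals are too wide. That needs forced balance within strata. The matching aim in the Trial design section suggests some restriction, since an unrestricted sequence within subgroups would not ensure such balance. But the article states no blocks, so miscalibration cannot be asserted.

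Third, the stated rationale links the stratum to pre-intervention functioning, and the ANCOVA already adjusts for the pre-intervention score. What remains is probably small, as step 5 shows near r = 0.89.

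Finally, a condensed article may leave its covariate list to an SAP. That does not dispose of the point: the article states an entry rule, and under it the design factor can be dropped.

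**Conclusion.** The point holds as one of pre-specification with a small efficiency gain. The plan stratifies on a factor and then leaves its place in the Cooking Task and Zoo Map models to a significance test. On the assumed q of 0.02 to 0.10, the simulated gain over a baseline-only model is roughly 0 to 3 power points. The gain over the plan as written is about half a point or less, if the stratum is indeed screened. Near the 0.89 reliability figure, the gain over baseline only is about one point or less.

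The direction is conservative at worst. The documents do not support the stronger reading that the trial is underpowered, because 123 reproduces at 80% without the stratum. The main benefit is that the adjustment set no longer depends on the data or differs between outcomes for this factor.

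**What to change.** State in the Statistical analysis section that the deficit stratum used at allocation is a fixed factor in the Cooking Task and Zoo Map ANCOVAs, whatever the screen shows. Add a stratum-by-time term to the mixed ANOVAs. The hierarchical regression needs no change on this account.

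First reconcile the subgroup labels. The Participants and recruitment and Randomization sections both attach mild to moderate deficit to composites below −2 SD and severe deficit to those at or above it, which looks reversed if lower scores mean worse function. Swapping the two labels would not alter the adjusted arm effect, but the coded factor must match the grouping actually used to draw envelopes. It would also help to say whether the sequence is blocked within strata, because that decides whether omitting the stratum would affect calibration or only efficiency.

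The cost is a line or two of wording and one degree of freedom in each ANCOVA. The stratum is determined before randomisation, so no new data are needed.

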### Study objectives and hypotheses

This RCT aims to address two fundamental questions: (1) is making errors actually beneficial in the learning process or is it better to avoid errors when training skills in rehabilitation? Specifically, does an EBL approach promote greater error self-regulation and self-awareness than ELL? And (2) is improvement in error self-regulation, behavioral competency and self-awareness following intervention related to better long-term social outcomes (for example, work, independence and relationships)?

It is hypothesized that, compared to participants in the ELL condition, participants in the EBL condition will demonstrate significantly greater gains in the following areas: (1) skills generalization on error self-regulation measures between pre-intervention and post-intervention assessment; (2) improvements in behavioral competency, awareness of deficits between pre-intervention and post-intervention assessment; and (3) improvements in long-term role participation and reduced support needs between pre-intervention, post-intervention and 6-month follow-up.

Secondly, it is hypothesized that greater skills generalization (that is, improved error self-regulation and behavioral competency) and pre/post changes in awareness of deficits will predict increased gains in long-term social outcomes (role participation and support needs) relative to pre-intervention assessment.

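### For the secondary outcomes, the three-visit group x time interaction does not match the pre-to-post hypothesis and cannot show a gain at 6 months; baseline-adjusted differences at named visits would do both

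*Protocol article*

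**What the plan says.** The Study objectives and hypotheses section tells the outcome sets apart by time. The second item, for behavioral competency and awareness, is "improvements in behavioral competency, awareness of deficits between pre-intervention and post-intervention assessment". The third, for role participation and support needs, names all three assessments and speaks of long-term change. All items predict greater gains under EBL.

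The Statistical analysis section sends all four domains to one mixed 2 x 3 ANOVA (group by pre, post and follow-up), in which "interaction effects will be examined to determine whether EBL is associated with greater gains than ELL relative to pre-intervention functioning". It names no visit-specific comparison for these outcomes. The same section handles the Cooking Task and Zoo Map part 1 differently: ANCOVA of the endpoint adjusted for baseline, followed by a 95% CI for the mean difference.

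The Sample size section uses "an estimated medium effect size (partial η^2^ = 0.061, PCRS discrepancy score") with "alpha level of 0.05, and power of 0.8". That effect comes from an earlier comparison "in improving awareness of deficits and behavioral competency between pre-intervention and post-intervention assessment", so it too is a two-visit effect.

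**The concern.** A two-arm, three-visit interaction is a 2-df test. It responds to any departure from parallel profiles: an advantage at post that persists, one that disappears, one that appears only at 6 months, or a reversal of the arms.

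For the awareness and competency hypothesis, the stated test therefore includes a visit that the hypothesis leaves out. The result can be significant with no pre-to-post difference, and a real pre-to-post difference that fades can be harder to detect.

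For role participation and support needs the three visits do match the hypothesis. Yet a significant interaction does not say that EBL is ahead at 6 months, and the Discussion treats long-term functional outcome as the goal that matters most.

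There is also a smaller matter of precision: the ANOVA uses baseline as one level of the time factor, not as a covariate.

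**Working it through.** **Inputs.** From Sample size: partial η² = 0.061, alpha 0.05, power 0.80, evaluable N = 123. From Measures: test-retest values of >0.85 (PCRS), 0.90 (SPRS) and 0.98 (CANS). Assumed, because the article does not give them: 1:1 allocation, compound symmetry, and correlation ρ between visits over the trial's intervals.

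**Step 1. The plan's own figure.** f² = 0.061/(1 − 0.061) = 0.0650; f = 0.255; d = 2f = 0.51 SD of change. With a noncentral F on 1 and N − 2 df and λ = N·f², λ at N = 123 is 123 × 0.06496 = 7.99 and power is 0.801. At N = 122 power is 0.797. So 123 reproduces exactly, as a 1-df two-group test of pre/post change.

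**Step 2. The planned 2-df interaction at N = 123.** Let the arm difference at pre, post and 6 months be δ times a shape (0, a, b), with δ = d·√(2(1 − ρ)) outcome SDs, so that δ is 0.51 SD of change. Then λ = (N/4)·SS·δ²/(1 − ρ) = (N/4)·SS·2d², where SS is the sum of squares of the shape about its mean. The correlation cancels: (123/4) × 2 × 0.2599 = 15.98, so λ = 15.98 × SS, on 2 and 242 df.

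| Pattern (pre, post, 6 months) | SS | λ | Power, 2-df interaction | Power, pre/post contrast | Power, pre/6-month contrast |
|---|---|---|---|---|---|
| Kept (0, 1, 1) | 0.667 | 10.65 | 0.836 | 0.801 | 0.801 |
| Lost (0, 1, 0) | 0.667 | 10.65 | 0.836 | 0.801 | 0.05 |
| Late only (0, 0, 1) | 0.667 | 10.65 | 0.836 | 0.05 | 0.801 |
| Half kept (0, 1, 0.5) | 0.500 | 7.99 | 0.711 | 0.801 | 0.289 |
| Reversed (0, 1, −1) | 2.000 | 31.96 | >0.99 | not needed | not needed |

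The first three rows are identical for the interaction, while the 1-df contrasts separate them. In the half-kept row the noncentrality equals that of the pre/post contrast (7.99) but is spread over 2 df, which is why power drops to 0.71.

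**Step 3. Baseline as covariate.** The variance of the arm difference relative to change from baseline is (1 − ρ²)/(2(1 − ρ)) = (1 + ρ)/2, so λ = 7.99/((1 + ρ)/2), on 1 and 120 df.

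| Assumed ρ | Variance ratio | λ | Power at post |
|---|---|---|---|
| 0.5 | 0.75 | 10.65 | 0.90 |
| 0.7 | 0.85 | 9.40 | 0.86 |
| 0.85 | 0.925 | 8.64 | 0.83 |
| 0.90 | 0.95 | 8.41 | 0.82 |
| 0.98 | 0.99 | 8.07 | 0.80 |

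The unadjusted pre/post contrast has 0.80 throughout. At the reported test-retest values the gain is small, and the adjusted contrast falls slightly below the interaction's 0.84 for a fully kept or fully lost gain.

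**The case against.** The strongest reply is that an interaction is normally followed by visit means and simple effects, and that a journal article may leave these to the analysis plan. That is fair as far as missing detail goes, and it is why this is a modest point. It does not cover the whole of it: the article itself names the interaction as the means of deciding whether gains are greater, and for awareness and competency that test spans a different period from the hypothesis.

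Several stronger readings are tempting, and the article does not support them:

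- *The plan fails to test its hypotheses.* Error self-regulation, including the primary outcome, is tested by baseline-adjusted ANCOVA, and the prediction hypothesis by hierarchical regression. The third item names all three visits, so the interaction is a relevant global test for it.
- *The ANOVA ignores baseline.* It does not. The interaction compares change from baseline and is valid under randomization. What is left is an efficiency difference that depends on ρ.
- *The omnibus test is the weaker one.* Not in general: it has 0.84 against 0.80 for the unadjusted contrast when the gain is fully kept or fully lost.
- *The ANOVA forces last observation carried forward.* The section states that rule for dropout in general, before naming any model. Nothing ties it to the ANOVA.
- *The sample size is too small because 123 reproduces only as a 1-df test.* Step 2 gives 0.84 at 123 for a fully kept gain, so this does not follow.

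**Conclusion.** The point holds as an improvement that costs almost nothing; it is not a flaw that invalidates the trial. For awareness and behavioral competency the stated test and the stated hypothesis cover different periods. For role participation and support needs the test is relevant but cannot show that a gain is present at 6 months.

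The problem is mainly one of interpretation: equal power of 0.84 for three clinically different patterns, and above 0.99 when the arms reverse. The power cost is specific to a partly fading gain (0.71 against 0.80). The benefit of covariate adjustment runs from worthwhile (0.90 at ρ = 0.5) to negligible (0.80 at ρ = 0.98).

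These figures rest on equal allocation, compound symmetry and assumed correlations. They also carry the PCRS discrepancy effect over to the other scales, which for the SPRS and CANS is illustrative only.

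**What to change.** In Statistical analysis, prespecify the baseline-adjusted EBL-ELL difference with a 95% CI:

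- at post-intervention for the PCRS relative rating, the PCRS discrepancy score and the AQ (awareness and competency hypothesis);
- at 6 months for the SPRS and CANS (role participation and support needs hypothesis).

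Use ANCOVA, as already planned for the Cooking Task, or a mixed model with baseline as covariate; either repairs the mismatch. Keep the 2 x 3 interaction as supportive.

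The cost is a change of wording: no extra assessments, participants or data. The change does not buy power for a gain that fades: with half kept, the 6-month contrast has about 0.29 unadjusted, and 0.37, 0.33 and 0.31 adjusted at ρ = 0.5, 0.7 and 0.85. It does give an estimate and interval at the visit on which each claim depends.

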#### Secondary outcomes

The Zoo Map Test from the Behavioural Assessment of Dysexecutive Syndrome [32] is a standardized neuropsychological test which examines the ability to plan, monitor performance and follow rules. In part 1, participants are asked to independently formulate and implement a plan to follow a route through a map without breaking specific rules. In part 2, participants follow a predetermined plan to complete the route. Although the profile score (1 to 4) will be calculated, the part 1 score (sequence score minus total errors) is the main index for analysis because this more directly assesses self-monitoring and self-regulation skills. The Zoo Map Test has been found to be a reliable and ecologically valid measure of planning and self-regulation [32,33].

The PCRS [25] is a well-established measure of awareness deficits and behavioral competency after TBI. The 30 items on the PCRS relate to participants’ current level of competency on activities of daily living (for example, meal preparation), interpersonal skills (for example, initiating conversations), behavioral (for example, controlling temper) and emotional function (managing depression) and cognitive abilities (for example, remembering conversations). Items are rated on a five-point Likert scale (1 = ‘can’t do’, to 5 = ‘can do with ease’). The discrepancy score between self-ratings and informant ratings on the PCRS is calculated to provide an index of self-awareness. Relatives’ ratings on the PCRS will assess skills generalization or broader behavioral competency. The PCRS has good test-retest reliability (*r* >0.85) and internal consistency (α >0.90) and established validity, including sensitivity to change [34].

The Awareness Questionnaire (AQ) [35] is a 17-item scale that assesses awareness of deficits across sensory, physical, cognitive, and behavioral domains. Unlike the PCRS, ratings on the AQ compare participants’ post-injury abilities on each item to their pre-injury functioning (that is, 1 = much worse, 3 = about the same, 5 = much better). Positive discrepancy scores (participant minus relative ratings) indicate impaired self-awareness. The AQ has sound psychometric properties [35] and has demonstrated sensitivity to change in the context of awareness interventions [18].

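### The regression of long-term SPRS and CANS on pre/post changes does not name treatment arm as a term, so an arm difference can appear as a link between change and outcome

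*Protocol article*

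**What the plan says.** The Protocol article's second hypothesis (Study objectives and hypotheses) is that better skills generalization and changes in awareness "will predict increased gains in long-term social outcomes (role participation and support needs) relative to pre-intervention assessment". The Statistical analysis section names the method and the predictors: "Hierarchical regression will be used to determine whether pre/post changes in awareness, error self-regulation and behavioral competency". For the outcomes and the adjustment, it asks whether those three change scores "predict long-term outcomes on the SPRS and CANS after controlling for pre-intervention functioning".

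The only other route by which a covariate can enter is the general screen: "Data will be screened to ascertain any state/site or therapist effects or the effects of demographic and clinical factors on outcome". Arm is in neither place. The same section does name group for the mixed ANOVA and makes it the comparison in the ANCOVA.

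Two of the predictors can come from one instrument. Under Secondary outcomes, "The discrepancy score between self-ratings and informant ratings on the PCRS is calculated to provide an index of self-awareness", and "Relatives’ ratings on the PCRS will assess skills generalization or broader behavioral competency". The Awareness Questionnaire (AQ) is a second awareness measure, and it too is scored as participant minus relative. The SPRS is rated from an interview with the relative, and the CANS from interviews with participant and relative.

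**The concern.** The change scores arise after randomization. The Background predicts that only EBL will generalize self-regulation skills and raise awareness, and both the Background and the hypotheses expect EBL to do better on long-term role participation and support needs. On the trial's own expectations, arm is therefore a common cause of predictor and outcome. In a pooled model without arm, part of the arm difference in outcome can be credited to the change scores even if, within each arm, people who change more do no better.

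The shared PCRS rating raises a separate question of attribution. When the relative's rating rises, the self-minus-relative discrepancy falls by the same amount, with no change in what the participant reports.

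At stake is the second of the trial's two stated questions: whether gains after training go with better social outcomes.

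**Working it through.** **1. The plan's own figure.** Partial η² = 0.061 gives f² = 0.061/0.939 = 0.0650, f = 0.255 and d = 2f = 0.51. For two groups, with a 1-df F test at α = 0.05 and noncentrality N·f² = 123 × 0.0650 = 7.99, power is 0.801 at N = 123 and 0.797 at N = 122. The stated 123 reproduces. Adding 10% gives 123 × 1.10 = 135.3, in line with 135. No error rate or power is stated for the regression.

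**2. Effect of leaving arm out.** Let arm shift one change score by e1 SD and the long-term outcome (given its baseline) by e2 SD, with no association within either arm. Allocation of 1:1 is assumed, since no ratio is stated. The pooled correlation created by arm alone is

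r = (e1·e2/4) / √[(1 + e1²/4)(1 + e2²/4)].

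The chance of p < 0.05 is about Φ(k − 1.96) + Φ(−k − 1.96), with k = r√123.

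Worked case, e1 = e2 = 0.51: r = 0.0650/1.065 = 0.061; k = 0.061 × 11.09 = 0.68; chance = 0.100 + 0.004 = 10.4%.

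| e1 (change) | e2 (outcome) | r | Formula, no arm | Simulation, no arm | Simulation, with arm |
|---|---|---|---|---|---|
| 0.51 | 0.20 | 0.025 | 5.9% | 5.7% | 5.0% |
| 0.51 | 0.30 | 0.037 | 6.9% | 6.7% | 5.1% |
| 0.51 | 0.51 | 0.061 | 10.4% | 10.4% | 4.8% |
| 0.80 | 0.51 | 0.092 | 17.5% | 16.9% | 5.2% |
| 0.90 | 0.64 | 0.125 | 28.4% | 28.0% | 4.7% |

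The simulation used 10,000 runs per row: outcome = 0.6·baseline + 0.8·e2·arm + 0.8·noise. Only the 0.51 for the change score comes from the protocol's planning effect. Every e2 is an assumption.

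**3. All three changes tested as a block** (4,000 runs, change shift 0.51). With a direct arm effect on the outcome of 0.2, 0.35 or 0.5 SD, the block is significant in 6.0%, 8.5% and 12.4% of trials without arm, and in 4.3%, 4.9% and 4.6% with arm. With no direct effect the figures are 5.3% and 5.0%.

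**4. Shared PCRS rating.** Let r be the change in the relative's rating and s the change in the self-rating, with equal SDs and correlation ρ. Then corr(r, s − r) = (ρ − 1)/√(2 − 2ρ), which is −0.71 at ρ = 0 and −0.59 at ρ = 0.3. In the block simulation the variance inflation factor was about 2.1 for each of the two PCRS predictors.

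Now let the outcome depend on r alone (assumed 0.3 per SD of r, residual SD 0.8, N = 123). The discrepancy entered without r is significant in about 79% to 81% of trials at ρ = 0 and about 63% at ρ = 0.3. With r in the same model it is significant in about 5%.

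**5. What adding arm does not cure** (same block test, no effect of any change on outcome):
- A common prognostic factor with loading 0.3 or 0.5: 21% or 87% significant without arm, 23% or 91% with arm.
- A shift in the relative's reporting that enters both the PCRS change and the outcome, loading 0.3 or 0.5: 12% or 56% without arm, 13% or 58% with arm.

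The loadings are assumptions. The document gives no SDs or correlations for change scores.

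**The case against.** The strongest reply is that this is one sentence on a secondary analysis in a condensed article, so arm may be in the full plan. That is possible, and the article does not say that arm is excluded. It does, however, state an adjustment set, and an analyst who followed that set would fit the model without arm. The comment is on the model as described.

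A second reply is that the hypothesis says "pre/post changes in awareness of deficits will predict increased gains in long-term social outcomes" and names no mediation analysis. If arm raises both quantities, the pooled association is real as a description. This stands in part: the rates above are false positives only for a link within arms. But the Discussion says the trial will examine whether gains after training carry through to long-term function, and a pooled association driven by arm would not answer that.

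A third reply is that the inflation needs an arm effect outside the measured changes, whereas the trial's rationale runs through those skills. This is correct, and it is why the size is modest. The 0.90 and 0.64 in the last table row are the Background's meta-analytic effects against wait list or conventional therapy. They are neither EBL-versus-ELL effects nor effects on SPRS or CANS, so 28% is an extreme case and not an expectation.

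A reader might infer that the shared relative rating by itself produces a false link to outcome. It does not. With both PCRS predictors in one model the false-positive rate stays near 5%, and entering self and relative ratings separately is the same model re-expressed. The article also does not say whether the PCRS or the AQ discrepancy will be the awareness predictor. Using the AQ would not remove the dependence on the relative.

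**Conclusion.** The point holds in a limited form. As described, the regression omits an expected common cause of its predictors and its outcome. For a 0.51 SD shift in a change score and assumed outcome shifts of 0.2 to 0.51 SD at N = 123, this raises the false-positive rate for a within-arm link from 5% to about 6% to 10%, and further under larger assumed shifts. Including arm restores about 5%. The result rests on 1:1 allocation and on arm acting on the outcome by a route other than the measured changes.

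The shared PCRS rating is a matter of attribution only. It can mislead if the discrepancy is entered in an earlier step or alone, and the article fixes neither the order of entry nor the awareness score.

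A reader might also infer that adding arm would make the regression a sound test of mechanism. The documents do not support that: the change scores are not randomized, and the relative informs the PCRS, the SPRS and in part the CANS. The primary Cooking Task ANCOVA and the group-by-time tests are not affected.

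**What to change.** - Enter treatment arm, with baseline SPRS or CANS, in the first block, before the change scores. Report the change-score coefficients given arm.
- State which awareness score is used. If it is the PCRS discrepancy, enter it in the same block as the PCRS relative rating, or enter self and relative ratings instead, and show both components.
- Report the result as an association, noting that prognosis and the common informant remain as explanations.

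The cost is one degree of freedom, a few sentences of analysis text and possibly a weaker association. No data collection changes.
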